**8.4 Control**

For participants in the control arm, 12-item HIV health behavioral messages tailored for MSM and nutrition messages targeted HIV/AIDS patients will be delivered every two weeks via SMS or WeChat based on their choices. All of these messages are adopted from National Center for AIDS/STD Control and Prevention and National Institute for Nutrition and Health.

**9. Outcomes and measures**

**9.1 Primary outcome**

The primary outcome is proportion of ART medication adherence within the previous month, which will be evaluated at baseline and in each follow-up. We will take both the percent adherence and dose-timing adherence into account to get a comprehensive assessment of ART adherence.

The ART adherence will be measured by two questions including “How many times have you missed taking your antiretroviral medication in the past month” and “how often did you take medications within one hour of prescribed dose-timing in the past month”. The first question requires participants to fill in the counts of missed doses in the past month. Options for the second question will include “never”, “occasionally”, “nearly half the time”, “more than half the time (most of the time)” and “all within the prescribed time”. We will categorize ART adherence as a binary variable. Those who never miss any doses or delay doses by one hour within the past month will be defined as “optimal adherence”. Otherwise, individuals will be regarded as “suboptimal adherence”.

**9.2 Secondary outcomes**

The secondary outcomes include CD4 T-cell counts, HIV viral suppression, HIV treatment adherence self-efficacy and quality of life. Among them, CD4 T-cell counts and HIV viral load will be obtained from medical records. The designated ART hospital regularly provides free CD4 T-cells and HIV viral load testing for all patients from March to June every year, the time of which is basically consistent with our planned second follow-up. In view of this, we will collect data in 2020 as baseline (pre-intervention) measurement and data in 2021 as post-intervention measurement. We will not collect additionally biological samples from participants in this study.

HIV treatment adherence self-efficacy will be measured using HIV Treatment Adherence Self-Efficacy Scale (HIV-ASES) at baseline and in each follow-up. The HIV-ASES was released by American CDC [36] and revised to Chinese version by Sun et al. [37]. The revised HIV-ASES-Chinese-Version includes 12 items measuring 2 dimensions (integration and perseverance). Respondents will rate on an 11-point Likert scale about how confident they are at performing behaviors related ART treatment (from 0= “not at all confident” to 10= “totally confident”). Scores of HIV-ASES range from 0 to 120, with higher score indicating better levels of self-efficacy. The revised HIV-ASES displays high reliability and validity (Cronbach’s alpha=0.876, 95%CI: 0.868-0.885) [37].

Quality of life will be evaluated by World Health Organization Quality of Life HIV short version (WHOQOL-HIV BREF) [38] at baseline and in each follow-up, which consists of 31 items covering 6 domains (physical, psychological, level of independence, social relationships, environment, and beliefs). The scores of WHOQOL-HIV BREF can be calculated within each domain or in total, ranging from 4 to 20 and 24 to 100 respectively, with higher score representing a higher level of quality of life.

**10. Sample size calculation**

The sample size was guided by a Gunn et al. [39]. The primary objective is to compare ART medication adherence at 6 months post allocation between the intervention arm and the control arm. The calculation was based on planned subgroup analysis, for that sample size would need to be larger to observe differences between study arms within strata than combined. Based on a previous SMS intervention in China [26], we calculated the sample size to detect a mean difference of 0.15 in proportions of achieving optimal ART adherence for text message subgroup. Due to no preliminary data, we hypothesized the difference will be no less than 0.15 for the instant message subgroup and instant message plus social media subgroup because participants in these two groups will receive consistent interventions and more incentives (cumulative clock-punching incentive), and consequently may have larger potential for adherence improvement.

Therefore, assuming a mean difference of 0.15 in proportions of achieving optimal adherence, two-sided alpha=0.05, 80% power and 20% loss to follow up, the sample size is 190 for text message subgroup. According to our pilot survey in another infectious disease hospital of Shandong Province, about two-thirds of PLWH are willing to choose instant message, and the others use text message or phone. Consequently, we anticipated that one-third of participants would choose text message in this study and extrapolated the total sample size was 570. The sample size calculation is conducted by PASS 15.

Due to the nature of the design, we cannot ensure participants choosing each of the three digital strategies in the anticipated proportion. And due to the limitation of cost and timeline, we will end up recruiting participants until reaching the total sample size (n=570) instead of satisfying the sample sizes of all three subgroups (each group n=190).

**11. Data collection**

Data will be collected using written questionnaires. At baseline, we will collect information about socio-demographic characteristics (including age, household, education, occupation, monthly income and marital status, etc), behavioral characteristics (including homosexual behaviors, sexual orientation disclosure, HIV status disclosure), HIV clinical knowledge, basic information of ART (including time and frequency of daily medication-taking, frequency of missed doses in the month, reasons of missed doses, side effects, etc), HIV treatment adherence self-efficacy, ART medication knowledge and quality of life. In follow-ups, we will collect information about ART adherence within the past month, HIV clinical knowledge, ART medication knowledge, HIV treatment adherence self-efficacy and quality of life through self-administered questionnaire. Besides, we will collect CD4 T-cell counts and HIV detectable viral load from medical records in the hospital.

A verification mechanism has been adopted to improve data quality. When a questionnaire is completed, investigators will check immediately to identify logical errors or missing data to verify with the participants. Participants will be reimbursed after the verification is completed.

**12. Analysis plan**

**12.1 Descriptive analysis**

All survey questionnaires will be coded and entered in to EpiData version 3.1 (EpiData Association, Odense, Denmark). Descriptive statistics will be used to compare the participants’ basic characteristics between the intervention and the control arm both in total and in each stratum. Student’s t tests will be used for normally-distributed continuous variables, Mann-Whitney U tests will be used for non-normally-distributed continuous variables, and Chi-square tests or Fisher’s exact probabilities will be used for categorical variables.

**12.2 Primary analysis**

The primary analysis will be performed on an intention-to-treat analysis utilizing generalized linear mixed models (GLMMs) to evaluate the effect of the differentiated digital intervention on the primary and secondary outcomes, which will include intervention status as fixed effects and individual participants with multiple measurements as random effects. The GLMMs will adjust for the baseline outcome measures (where appropriate), stratification factors (i.e. text message, instant message, instant message plus social media group), and time (baseline, 3 months and 6 months). Baseline variables significantly associated with the outcomes and found to be imbalanced between intervention arm and control arm will also be considered for adjustment in the regression models. The risk ratio (RR) or mean difference (MD) of the outcomes between study arms will be reported as estimated intervention effects with 95% confidence intervals and two-sided P values.

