**3.2 Objectives**

**Primary objective**: To determine if the differentiated digital intervention can improve ART adherence among MSM living with HIV at 6 months compared to the control arm.

**Hypotheses 1**: The differentiated digital intervention is superior in improving ART adherence compared to the control arm.

**Secondary objectives**: To determine (1) whether CD4 T-cell counts, HIV viral suppression, HIV treatment adherence self-efficacy and quality of life differ between the intervention arm and the control arm at 6 months; (2) whether the outcomes (i.e. ART adherence, CD4 T-cell counts, HIV viral suppression, HIV treatment self-efficacy and quality of life) differ between the two study arms within each of the three subgroups (i.e. text message subgroup, instant message subgroup, and instant message plus social media subgroup)

**Hypotheses 2**: The differentiated digital intervention is superior in improving CD4 T-cell counts, HIV viral suppression, HIV treatment adherence self-efficacy and quality of life. Text message-based intervention, instant message-based intervention, and instant message plus social media intervention are superior in improving the health outcomes.

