**8. Interventions**

Participants in the intervention arm will receive interventions within six months post allocation, which include health messaging, medication reminders, peer education and online group discussion. The health messages include 12-item ART medication messages and 6-item HIV clinical messages, which are adopted from national AIDS antiviral treatment manual or authoritative websites of China’s CDC, and checked by AIDS experts from local hospital and CDCs. The 12-item ART medication messages include management of side effects, solutions for missing doses, definition of drug resistance, etc. The 6-item HIV clinical messages include explanations of some HIV terms (e.g. “window period of HIV infection”, “CD4 T-cell counts”, “HIV viral load”), precondition of ART initiation, etc. We will deliver ART medication messages every two weeks and HIV clinical messages every month respectively. Second, daily medication reminder service (SMS platform or WeChat mini-program) is designed to serve for those who need the service (optional for participants). The reminders will not include words regarding “HIV” or “AIDS” to avoid potential privacy disclosures. Third, peer education stories will be used to improve ART adherence and health perception. We will deliver peer education service every two weeks after the first follow-up (i.e. 3 months post allocation). The ways of intervention delivery are differentiated for each subgroup, the details of which are as followed.

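### The primary mixed model gives one intervention effect pooled over visits, while the objective and sample size concern the effect at 6 months

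*Protocol*

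**What the plan says.** Protocol section 3.2 states the trial's main aim in these words: "To determine if the differentiated digital intervention can improve ART adherence among MSM living with HIV at 6 months compared to the control arm". Section 10 sizes the trial on the same target: "The primary objective is to compare ART medication adherence at 6 months post allocation between the intervention arm and the control arm".

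Section 12.2 describes the primary analysis as generalized linear mixed models "which will include intervention status as fixed effects and individual participants with multiple measurements as random effects". Time appears among the adjustment terms, with the levels "time (baseline, 3 months and 6 months". On baseline values it says: "The GLMMs will adjust for the baseline outcome measures (where appropriate", a qualifier that it does not explain. On reporting it says: "The risk ratio (RR) or mean difference (MD) of the outcomes between study arms will be reported as estimated intervention effects". It names no arm-by-time term, no 6-month contrast and no visit to which the reported effect belongs.

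Two design facts bear on this. Under section 7, randomisation follows the baseline survey. Under section 8, one component of the package starts late: "We will deliver peer education service every two weeks after the first follow-up", that is, after month 3.

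**The concern.** With time entered only as an adjustment, a single intervention coefficient is a weighted average of the arm differences at all visits that serve as responses. It equals the 6-month effect only if the effect is the same at all of them.

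The design gives reasons to doubt that:

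- **Baseline.** It precedes allocation, so the true arm difference there is zero. Listing baseline as a level of time makes sense only if baseline is a response row, and section 12.2 also provides for adjusting for the baseline outcome. These two uses need reconciling.
- **Month 3.** Peer education has not begun, and section 9.1 measures adherence over the preceding month. Adherence reported at 3 months therefore cannot reflect that component.

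At stake is the headline estimate. It could understate what the full package achieves at 6 months and would answer a question other than the one in section 3.2.

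**Working it through.** **1. The plan's own figure.** Section 10 gives a difference of 0.15, two-sided alpha 0.05, 80% power, 20% loss, and 190 for the text message stratum. It gives no control proportion. Assuming 0.80 against 0.95, with mean proportion 0.875 and the pooled-variance formula:

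n per arm = [1.96 × √(2 × 0.875 × 0.125) + 0.8416 × √(0.80 × 0.20 + 0.95 × 0.05)]² / 0.15² = (0.917 + 0.383)² / 0.0225 ≈ 75.1, rounded up to 76.

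Then 2 × 76 / 0.8 = 190, and 3 × 190 = 570. The figure reproduces as a comparison at one visit. The present point does not show the sample size to be wrong.

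**2. Simple averages.** Take a true difference of 0 at baseline and 0.15 at 6 months, with three assumed values at 3 months and equal weights.

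| 3-month effect | Baseline, 3 and 6 months | 3 and 6 months only |
|---|---|---|
| 0.15 (full) | (0 + 0.15 + 0.15)/3 = 0.10 | (0.15 + 0.15)/2 = 0.15 |
| 0.075 (half) | (0 + 0.075 + 0.15)/3 = 0.075 | (0.075 + 0.15)/2 = 0.1125 |
| 0 (none) | (0 + 0 + 0.15)/3 = 0.05 | (0 + 0.15)/2 = 0.075 |

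**3. Large-sample fit of the logistic mixed model.** A random-intercept logistic model was fitted to exact expected cell probabilities, with an arm main effect, three-level time and no baseline covariate. Fitted probabilities were averaged over the random intercept to give the implied 6-month difference. Assumed inputs: control proportion 0.6, 0.7 or 0.8 at every visit; random-intercept SD 1.0, 1.5 or 2.5.

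| 3-month effect | Main-effect model | Arm-by-time terms, arms equal at baseline |
|---|---|---|
| full | 0.083-0.097 | 0.150 |
| half | 0.060-0.072 | 0.150 |
| none | 0.037-0.047 | 0.150 |

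At a control proportion of 0.80 the main-effect model implies a risk ratio of about 1.04-1.10, against a true 0.95/0.80 = 1.19.

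**4. Simulation with the baseline covariate.** Inputs: N = 570, 20% lost at 6 months (both from section 10); control proportion 0.70 and random-intercept SD 2 (both assumed). The true 6-month log odds ratio is 1.37. Results are in the order full, half, none.

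- *Baseline both a response row and a covariate:* 0.84, 0.60 and 0.37 (200 runs each), which is 0.84/1.37 = 61%, 0.60/1.37 = 44% and 0.37/1.37 = 27% of the truth. Power in two smaller sets of runs was about 100%, 100% and 60% (60 runs each) and about 100%, 100% and 65% (40 runs each).
- *Baseline a covariate only, responses at 3 and 6 months:* 1.39, 0.95 and 0.50; power about 100%, 97% and 58% (60 runs each).
- *6-month contrast:* 1.38-1.39, with power of at least 99% in all three cases.
- *No intervention effect:* type I error of the pooled model 5.6% (500 runs).

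The small sets are approximate: the Monte Carlo standard error is √(0.60 × 0.40/60) = 0.063 for the 60% figure and √(0.65 × 0.35/40) = 0.075 for the 65% figure.

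**The case against.** Section 12.2 is a protocol summary, not a model equation. Interactions, contrasts and coding are often left to an analysis plan, and none is shown here. That stands as a caution: the protocol does not rule out an arm-by-visit term. But the point does not rest on missing detail. The section lists the model's terms and one reported effect, and these do not deliver the 6-month comparison set in sections 3.2 and 10.

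A reader might infer that the plan certainly uses baseline twice, or certainly averages in a visit before randomisation. The text does not support that certainty. The qualifier on baseline adjustment allows baseline to be a covariate only. Coding intervention status as zero for everyone at baseline would also remove that dilution, though the protocol does not say this is done. Either way a 3-and-6-month average is left.

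A reader might also infer that an effective package would probably be reported as null. That is too strong. Power of 89%, 62% and 29% on the three paths comes from a variant without the baseline covariate. It should not be attributed to a plan that provides for that covariate, with which power is near 100% on two of the three paths. The third path, no effect at all at 3 months, is extreme: messages and optional reminders run from the start, and only peer education waits.

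Finally, section 9.1 has the outcome evaluated at every follow-up, so a pooled effect after randomisation could be a legitimate target. It is not the one that the protocol declares.

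**Conclusion.** The point holds as a mismatch between the stated model and the stated objective. On the literal reading, a 6-month difference of 0.15 is reported as roughly 0.04-0.10, depending on how much of the effect is present at 3 months. With baseline as a covariate only, it is reported as roughly 0.075-0.15, with no loss if the effect is already full at 3 months.

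The harm is mainly an attenuated estimate that answers a different question. False positives are not inflated. With the baseline covariate, serious power loss is confined mainly to the case of little effect at 3 months.

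The sizes rest on assumed control proportions, random-intercept SDs and effect paths that the protocol does not give. All the paths have a 3-month effect no larger than the 6-month effect. If the effect waned after month 3, a 3-and-6-month average would overstate the 6-month effect instead.

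**What to change.** In section 12.2, add an arm-by-visit term and declare the 6-month arm contrast the primary estimate, reported as the planned risk ratio (or mean difference for continuous outcomes). A risk difference is optional.

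Use baseline once only, in one of two ways:

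- as a covariate, with the 3- and 6-month records as the responses; or
- as a response row, with the arms constrained equal at baseline and no baseline covariate.

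These are alternatives, not identical models, so name one in advance. Keep the three-level stratum and the participant random effect. Apply the same form to HIV-ASES and WHOQOL-HIV BREF, which follow the same visit schedule.

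The cost is a wording change and one model term, with no new data and no additional participants.

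### The three-visit GLMM is prescribed for CD4 and viral suppression, which have only one value before and one after allocation; either way of fitting it gives a poorly defined or diluted result

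*Protocol*

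**What the plan says.** Section 12.2 of the protocol sets out a single model family "to evaluate the effect of the differentiated digital intervention on the primary and secondary outcomes". Its fixed effect is intervention status, and its random effects are "individual participants with multiple measurements as random effects". On covariates it says "The GLMMs will adjust for the baseline outcome measures (where appropriate"), and it adds the stratification factor and "time (baseline, 3 months and 6 months"). No arm-by-time interaction is listed. Results are to be reported as a risk ratio or a mean difference; no link function is named.

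Section 9.2 sets the schedule for the two laboratory outcomes. The hospital "regularly provides free CD4 T-cells and HIV viral load testing for all patients from March to June every year", and from those records "we will collect data in 2020 as baseline (pre-intervention) measurement and data in 2021 as post-intervention measurement". It also states: "We will not collect additionally biological samples from participants in this study". By contrast, adherence (section 9.1) and the self-efficacy and quality-of-life scales (section 9.2) are measured at baseline and at both follow-ups. Sections 12.1 to 12.5 give no separate model for CD4 or viral suppression.

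**The concern.** The model assumes three measurements per man; these two outcomes have two, and none at 3 months. An analyst must therefore depart from the text, and the two obvious departures answer different questions. One leaves a single outcome row per man, which cannot carry a participant random effect. The other keeps two rows, but then the only treatment term includes a pre-intervention comparison in which no effect can exist.

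This matters because CD4 and viral load are the only outcomes taken from medical records. Participants know which service they receive (section 7), and the primary outcome is self-reported (section 9.1). Hypothesis 2 in section 3.2 claims superiority on both laboratory outcomes.

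**Working it through.** The plan gives no figure of its own for these two outcomes. Its sample size concerns adherence and is not used, except that 570 × 0.8 = 456 men serves as an illustrative number followed up.

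**1. The 3-month level.** Take fixed effects for intercept, arm, two stratum indicators and two time indicators (3 and 6 months): 6 columns. With records only at baseline and 6 months, the 3-month column is all zeros and the design has rank 5 of 6. Dropping that level restores full rank, so this alone is easily repaired.

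**2. Baseline as covariate (one row per man).** The CD4 model is

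y(2021) = b0 + b1·arm + b2·y(2020) + stratum + u + e, with Var(u) = su² and Var(e) = se².

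Each man contributes one residual, with variance su² + se². Only that sum enters the likelihood.
- The information matrix for (su², se²) has rank 1 of 2.
- In simulated data for 456 men, the log-likelihood is −2844.44 whether 0%, 25%, 50%, 75% or 90% of the variance is given to u.
- The estimate of b1, the mean difference, does not change.

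For viral suppression with a logit link, the marginal probability in an arm is p = E[expit(a + s·Z)], with Z standard normal. For any s, a value of a can be found that gives the same p, so the likelihood is flat in s. In a simulated example it is −175.84 for every SD tried from 0.01 to 4. Assume observed suppression of 88% and 94% (not in the protocol). Solving for a in each arm gives:

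| Random-intercept SD | a at 88% | a at 94% | Odds ratio exp(difference) |
|---|---|---|---|
| 0.01 | 1.992 | 2.752 | 2.14 |
| 1 | 2.337 | 3.166 | 2.29 |
| 2 | 3.127 | 4.171 | 2.84 |
| 3 | 4.097 | 5.438 | 3.82 |
| 5 | 6.243 | 8.266 | 7.56 |

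The first row matches the crude odds ratio, (0.94/0.06)/(0.88/0.12) = 2.14. The crude risk ratio is 0.94/0.88 = 1.07 throughout.

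**3. Baseline as an outcome row (two rows per man).** The random intercept can now be estimated.
- The variance information has rank 2 of 2.
- A simulated CD4 model with true SDs of 150 (between men) and 100 (within men) converges to 143 and 98.
- In a logistic example with true SD 2, the profile log-likelihood peaks there: −367.34, against −373.96 at SD 1 and −371.03 at SD 3.

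The treatment term is the problem. With arm and time but no interaction, and complete two-row data, the arm coefficient is

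b(arm) = ½ × [(arm difference in 2020) + (arm difference in 2021)].

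Randomization makes the first difference zero in expectation. If the true 2021 effect is d, the expected coefficient is ½ × (0 + d) = d/2. For an assumed CD4 effect of 40 this is 20. Simulation with 456 men and within-man correlations of 0.5 and 0.7 agrees: about 20 from the mixed model and about 40 from ANCOVA.

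**The case against.** The best defence is that section 12.2 describes a common framework and can be adapted. Baseline adjustment is only conditional, baseline is a listed time level, and trimming a time level without data is routine. Much of this stands. A reader might infer that the pre/post schedule by itself makes the random effect unidentifiable. It does not: that happens only when the 2020 value moves to the covariate side, and step 3 shows that two rows are enough. The defence still fails to rescue the text, because the two-row route brings in the diluted arm term. Using baseline both as a row and as a covariate is no remedy. Nor is this merely detail left to a statistical analysis plan: the protocol names a model and extends it to these outcomes without exception.

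A reader might also take 2.1 to 7.6 as the range of the ratio that the trial would report. The protocol promises a risk ratio and names no link, so that range does not describe the promised measure. In a log-link Poisson mixed model with one row per man (228 per arm assumed; 201 and 214 suppressed), the log-likelihood is −453.9 near SD 0, −470.3 at SD 0.3 and −586.4 at SD 1. The fit therefore goes to SD 0 with a risk ratio of 214/201 = 1.065, and forcing SD 1 gives only 1.08.

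Finally, one might expect the viral suppression model to fail to converge. The calculations above do not test that for the one-row model, so it cannot be claimed.

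**Conclusion.** The point holds in a limited form. The stated model does not fit the stated data for CD4 and viral suppression, and the plan names no exception. With the 2020 value as covariate, the participant random effect is unidentified. This is harmless for the CD4 mean difference and for a log-link risk ratio of the kind checked, but consequential for a logit-link estimate of suppression. With the 2020 value as an outcome row, the stated arm term gives about half the effect. That result is exact in expectation for a continuous outcome with complete two-row data, and approximate otherwise.

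The odds-ratio range is illustrative and rests on assumed rates of 88% and 94% and on a logit link. The CD4 effect of 40 and the correlations are also assumptions, but the factor of one half does not depend on them. Two secondary outcomes are affected. Nothing here bears on the primary outcome's three-visit schedule or on the sample size. The change should be made, because two analysts following section 12.2 could report materially different results for the only record-based outcomes.

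**What to change.** In section 12.2, take CD4 and viral suppression out of the three-visit model and add two sentences:
- 2021 CD4 is analysed by ANCOVA on arm, 2020 CD4 and stratum, reporting the mean difference.
- 2021 suppression is analysed by modified Poisson regression with robust variance on arm, 2020 suppression status and stratum, reporting the risk ratio.

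Neither model has a participant random effect. The mixed model remains for adherence, HIV-ASES and WHOQOL-HIV BREF.

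An acceptable alternative is a two-level time model with the 2020 value as an outcome row, not also as a covariate, reporting the arm-by-time contrast. It addresses the same question. In one simulated CD4 data set its standard error was 13.0, against 11.7 for ANCOVA, and for suppression it would need a link that yields the promised risk ratio.

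The cost is two sentences and simpler models. No new data are needed and no sample-size figure changes.
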